**Foley Catheter for Induction of Labor at Term:**

**a Multi-Center Randomized Controlled Trial**

**(Study Protocol)**

**Protocol Submission To**

**Nanjing Drum Tower Hospital**

**Institutional Review Board**

**January 2013**

**Principal Investigator**

**[name]**

**1. Background**

Labor induction is a frequently used method in the management of high-risk pregnancy. Both medical and mechanical methods have been applied to induction of labor. Foley catheter insertion has been proved as effective as prostaglandins in achieving delivery within 24 hours without increasing the risk of cesarean section [1]. In the mean time, Foley catheter use provides the advantage of low risk of hyperstimulation and low cost of the devices.

There was considerable heterogeneity in mechanical ripening protocols in literature. Balloon inflation sizes of 30-80mL have been compared with inconsistent results regarding induction-to-delivery time and risk of operative delivery [2-4]. There was also no consensus on the time limitation for exposure to extra-amniotic Foley catheter balloon. Some practitioners set a maximum time limit [2-3], while others wait until spontaneous expulsion of the balloon catheter [4-5]. Cromi reported cutting the maximum time for cervical ripening (from 24 to 12 hours) would increase the proportion of women who deliver vaginally within 24 hour after Foley catheter insertion [6].

In our previous research, we have proved that Foley catheter can be safely used in term labor induction. However the vaginal delivery rate within 24 hours is relatively low with an 80mL balloon for a maximum of 24 hours ripening. Our present study, therefore, aims to determine whether different time length of ripening (12 vs. 24 hours) and different balloon size (30 vs. 80 mL) would influence the efficacy of a transcervical Foley catheter used in labor induction.

**2. Aims of the trial**

The objective of this trial is to explore the optimal balloon size and ripening time when Foley catheter is used in term labor induction. Specifically we aim to study:

1. The effect of 2 balloon sizes and 2 ripening time limits on the outcomes of induction when Foley catheter is used.
2. Maternal and neonatal complications in Foley catheter balloon induction.
3. Labor patterns of induced vs. spontaneous labor.

**3. Study Design**

1. **Study Design** It is an open-label, randomized, controlled trial in a multi-center setting. Participants will be randomly allocated to one of four parallel groups, in 1:1:1:1 ratio, to receive either one of four treatments: (1) 30 mL balloon for a maximum of 12 hours, (2) 30 mL balloon for a maximum of 24 hours, (3) 80 mL balloon for a maximum of 12 hours, (4) 80 mL balloon for a maximum of 24 hours. Neither the investigator nor the participants are blind to the assignment.
2. **Randomization** The randomization sequence is computer-generated with variable blocks in 1:1:1:1 allocation for each arm by the statistician ([name]). Since 95% of women undergoing labor induction in our district are nulliparous, we will not stratify women according to parity. The randomization sequence will be placed into numbered opaque envelopes by two doctors uninvolved in the trial before the initiation of the study. None of the clinical investigators will have access to the schedule until completion of the study.
3. **Inclusion /Exclusion Criteria** Women scheduled for labor induction will be screened for eligibility. Inclusion criteria are gestational age ≥ 37 weeks; singleton gestation with cephalic presentation; intact membranes; reactive non-stress test and Bishop’s score < 6. Women less than 18 years, with multiple pregnancy, abnormal pelvimetry, abnormal presentation, placenta previa, vaginal infection, intrauterine fetal death, or GBS positive will be excluded.
4. **Primary Outcome** The primary outcome is vaginal delivery within 24 hours.
5. **Secondary outcomes** Secondary maternal outcomes are cesarean section rate, instrumental vaginal delivery, indications for operative delivery, induction-to-delivery time, induction-to-active phase time, epidural analgesia, oxytocin use, uterine hyperstimulation, chorioamnionitis, postpartum hemorrhage (blood loss >500ml within 24h after delivery)，postpartum transfusion, cervical dilation and station. Secondary neonatal outcomes include birth weight, the rate of Apgar scores of less than 7 at 5 minutes and neonatal admission.
6. **Duration of the Project** We will recruit participants between February 2013 and June 2014.
7. **Sample Size** Our previous study using an 80mL balloon with a maximum of 24 hours indicated a vaginal delivery rate in 24 hours of 28.1%[7]. A review of studies of various balloon sizes and ripening time showed a vaginal delivery rate within 24 hours ranges from 48% to 66%. Under this scenario, we assumed that by revising the Foley catheter induction protocol we could achieve a clinically significant increase in vaginal delivery within 24 hours. Thus planned sample size for this investigation was 126 patients each treatment group to show an increase in vaginal delivery rate within 24 hours from 28% to 48% with a two-sided test (α error=5%, power=80%). Formula: $n=2\lambda/{(2\sin^{-1} \sqrt{p_{max}}-2\sin^{-1} \sqrt{p_{min}})}^{2}$
8. **Labor patterns** To investigate the progress of labor in women induced with Foley catheter versus spontaneous labor, we will prospectively collect the information of women with spontaneous onset of labor and vaginal delivery in a 1:1 ratio in Nanjing Drum Tower Hospital. Women will be eligible as control group if they are nulliparous, singleton pregnancy in vertex presentation, less than 2 cm dilated at admission, and have spontaneous onset of labor. We will exclude women who deliver preterm, have fetus with congenital anomalies, or deliver by cesarean section. Participants need to sign written informed consent and clinical data will be used for research. Maternal age will be matched and difference of gestational age at delivery should be less than 7 days.

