**4. Settings**

| Institutions | No. Of participants to recruit |
| --- | --- |
| Nanjing Drum Tower Hospital (leader institution) | 296 |
| Wuxi Maternal and Child Health Hospital | 52 |
| Taixing People's Hospital | 52 |
| The First People's Hospital of Kunshan | 52 |
| Jintan People's Hospital | 52 |

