**E. Management of Labor**

When a woman is in active labor, maternal heart rate, blood pressure and temperature will be recorded every 6 hours, fetal heart rate and uterine activity will be continuously recorded with fetal heart monitor. The attending doctors will make clinical decision when there is an abnormal fetal heart tracing or failure to progress.

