**7. Statistical Analysis**

Statistical analysis of outcomes data will be performed with SPSS 17.0. Data will be analyzed on an intention-to-treat basis. Normally distributed data will be presented as means with SDs; skewed distributions will be presented as medians with IQRs or medians with ranges. Categorical outcomes will be summarized using frequency distributions. For quantitative data, ANOVA or rank sum test will be used. For categorical data, we will calculate p values with Chi-square or Fisher exact tests. For time-to-delivery data, we will construct Kaplan-Meier survival curves and calculate log-rank test and p values. A probability value of 0.05 will be used as the cut-point for significance.

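### The protocol does not say whether randomisation lists and envelopes are made by hospital, and its listed tests have no centre term; the cost is chance imbalance and lost precision, not bias

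*Protocol*

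**What the plan says.** Section 3, item 1 describes an open-label, multi-centre trial with four arms in equal ratio. Item 2 says "The randomization sequence is computer-generated with variable blocks in 1:1:1:1 allocation for each arm". On stratification it says only "we will not stratify women according to parity", because almost all induced women in the district are nulliparous. On concealment: "The randomization sequence will be placed into numbered opaque envelopes by two doctors uninvolved in the trial before the initiation of the study". Hospital is not mentioned, either as a stratum or in how the envelopes are numbered and shared out.

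The table in section 4 names five hospitals: the lead site with 296 women and four others with 52 each.

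Section 6.E states: "The attending doctors will make clinical decision when there is an abnormal fetal heart tracing or failure to progress".

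Section 7 states: "For categorical data, we will calculate p values with Chi-square or Fisher exact tests". It also lists ANOVA or rank sum tests for quantitative data and Kaplan-Meier curves with a log-rank test for time to delivery. None is described with a centre term. The checklist in Appendix 1 and the case report form in Appendix 2 have a patient ID but no field for hospital.

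**The concern.** The primary outcome is vaginal delivery within 24 hours, so a cesarean counts as a failure. Decisions on abnormal tracings and on arrested labour rest with each hospital's doctors, so event rates may well differ between hospitals. The allocation is open. One hospital supplies 296/504 = 58.7% of the women, 5.7 times as many as each of the others; the four smaller ones together supply 208/504 = 41.3%.

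Sequence generation and envelope numbering belong in the protocol and cannot be repaired once envelopes are opened. As written, a reader cannot tell whether the arms will be balanced within each hospital or only overall. The forms do not visibly record what a later centre-adjusted analysis would need. At stake is how far a difference between arms could reflect a different mix of hospitals, and how much precision is lost by leaving centre out of the test.

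**Working it through.** **1. The plan's own figures.** Section 3, item 7 gives n = 2λ/(2 arcsin√0.48 − 2 arcsin√0.28)². The bracket is 0.4156. For four groups (3 df), two-sided 5% and 80% power, λ = 10.90, so n = 2 × 10.90/0.4156² ≈ 126.2; the protocol states 126. The hospital targets agree: 296 + 4 × 52 = 504 = 4 × 126. Each divides by four: 296/4 = 74 and 52/4 = 13 per arm.

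**2. Balance under three ways of sharing the envelopes.** These are simulations with 4,000 runs each. Assumptions not in the protocol: block sizes 4 and 8, and hospitals recruiting in random order. The gap is the largest minus the smallest arm, in women.

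| Envelope supply | Mean gap, 52-woman hospital | Mean gap, lead hospital | Largest difference between arms in lead-hospital share: mean (95th percentile) |
|---|---|---|---|
| One list, opened in order of enrolment across hospitals | 7.0 | 11.3 | 9.0 points (15.9) |
| One list, consecutive runs sent to each hospital | 0.9 | 0.5 | 0.6 points (1.6) |
| Separate blocked list per hospital | 0.5 | 0.5 | 0.8 points (1.9) |

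**3. Effect on an arm contrast.** Under the shared list, the difference in lead-hospital share between two given arms has SD 6.1 points. The protocol gives no hospital-specific event rates. If the other hospitals' rate differed from the lead's by 20 points (an assumption), a 1 SD imbalance would move a contrast by 0.061 × 20 = 1.2 points. The 95th-percentile largest gap would move it by 0.159 × 20 = 3.2 points. The planned effect is 20 points.

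**4. Type I error of the unadjusted chi-square.** 3,000 runs each, lead rate 28%, the other four hospitals higher by the amount shown; Monte Carlo standard error about 0.4 points.

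| Centre difference | 0 | 20 points | 40 points |
|---|---|---|---|
| Shared list | 4.9% | 5.0% | 5.9% |
| Separate lists | 4.5% | 4.2% | 2.3% |

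Under the shared list each arm is a random sample of the same mix of hospitals, so the nominal level is expected. A repeat with 2,500 runs gave 5.1%, 5.7% and 5.4%.

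**5. Why balance makes the unadjusted test conservative.** The unadjusted test uses the total outcome variance T = p(1−p), although balanced allocation has already removed the between-hospital part B = 0.587 × 0.413 × d².

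- d = 0.20: p = 0.28 + 0.413 × 0.20 = 0.363; T = 0.231; B = 0.0097; B/T = 4.2%.
- d = 0.40: p = 0.445; T = 0.247; B = 0.0388; B/T = 15.7%.

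The 3-df critical value of 7.815 is in effect raised to 7.815 × T/(T−B), which gives true levels of 4.3% and 2.6%. This agrees with the simulated 4.2% and 2.3%.

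**6. Precision gained by adjusting.** A centre-stratified test multiplies the noncentrality by about T/(T−B). Starting from λ = 10.90 (80.0% power), power becomes 81.8% at d = 0.20 and 86.9% at d = 0.40. Simulations gave about 2 points or less at d = 0.20. At d = 0.40 they ranged from under 3 points, where power already exceeded 90%, to 8–10 points.

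**The case against.** The strongest reply is that the protocol never says one unstratified list serves all five hospitals. A reader might infer that from the singular noun and the silence on centre, but neither proves it. Targets that all divide by four are equally compatible with blocks within hospital, though they do not prove that either. This stands: the point is that the method is unstated, not that a wrong method was chosen.

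A reader might also infer that dividing one numbered list among hospitals destroys balance. It does so only if envelopes are drawn in an interleaved way. Consecutive runs cut at most one block at each boundary and leave a mean gap of 0.9 women at a small hospital.

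A tempting illustration is a 7 v 19 split at a 52-woman hospital, since each count lies within 2 SD of 13 (SD = √(52 × 0.25 × 0.75) = 3.12). That assumes unblocked allocation, whereas the protocol specifies blocks. As a difference between two arms it is also 12/√(52 × 0.5) = 12/5.1 = 2.35 SD, which is a tail case.

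Systematic bias and an inflated false-positive rate are further inferences that the figures do not support.

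Finally, centre adjustment is often left to an analysis plan, and one may exist. That limits the analysis part: unadjusted tests are not an error, and a centre term is an improvement on the test named in section 7. It does not answer the randomisation part or the missing hospital field.

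**Conclusion.** The point holds as a gap in the randomisation text together with a less efficient stated analysis. The protocol does not say whether the sequence and envelopes are generated by hospital, and the tests it lists have no centre term, although the hospitals are very unequal in size and local decisions bear on the primary outcome.

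The consequence depends on which method was meant. With a shared list, balance by hospital is left to chance. With allocation balanced by hospital, the unadjusted test is valid but conservative when centre rates differ. A centre term helps in both cases: little if centre rates differ by 20 points, noticeably if they differ by 40.

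These sizes rest on assumed block sizes, recruitment order and centre rates, none of which the protocol gives. The change is worth making because it is cheap and the allocation part cannot be corrected later; the trial's validity is not in doubt on this account.

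**What to change.** - **Section 3, item 2:** state that the statistician generates a separate variable-block list, with its own numbered envelope series, for each of the five hospitals. The existing targets fit: 74 per arm at the lead hospital and 13 per arm at each of the others.
- **Appendix 2:** add a hospital code, or state that the patient ID encodes it.
- **Section 7:** analyse the primary outcome with centre as a factor (Cochran-Mantel-Haenszel test or logistic regression) and time to delivery with a log-rank test stratified by centre. If an analysis plan already does this, bring section 7 into line with it.

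If envelopes have already been issued, make only the form and analysis changes and record how the envelopes were divided.

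The cost is a little statistician time, one form field and a few lines of text. One small downside is that late allocations at a small open-label hospital become slightly easier to guess. Keeping block sizes variable and undisclosed to the sites limits this.

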**Appendix 2. Case Report Form for Balloon Induction**

| Year of Birth | (m/year) | | | Patient ID | | | |  |
| --- | --- | --- | --- | --- | --- | --- | --- | --- |
| Height | cm | | | Wt before Delivery | | | | Kg |
| GA | w d | | | G/P | | | |  |
| Indication | - □Prolonged gestation - □FGR - □Medical | | | - □GDM／DM   □Oligohydramnion | | | | - □PIH   □ICP  □Other |
| Group | □ 30mL Balloon×12h  □ 80mL Balloon×12h | | | □30mL Balloon×24h  □80mL Balloon×24h | | | |  |
| Time of induction |  | | | Bishop before induction | | | |  |
| Time of Removal |  | | | Bishop after induction | | | |  |
| Indication for | □Spontaneous | | | □Time limit reached | | | | □Abnormal CTG |
| Balloon Removal | □Hyperstimulation | | | □Rupture of membrane | | | | □Abnormal Bleeding |
|  | □Active labor | | | □Discomfort | | | |  |
| Induction after | □Amiotomy | | | Time | | | |  |
| Balloon Removal | □Oxy  □Max dose of Oxy | | | Time | | | |  |
|  | □Other | | | Time | | | |  |
| Labor patterns |  | | |  | | | |  |
| Time | | | Dilation of cervix | | | Decadence of presentation | | |
|  | | |  | | |  | | |
|  | | |  | | |  | | |
|  | | |  | | |  | | |
|  | | |  | | |  | | |
|  | | |  | | |  | | |
|  | | |  | | |  | | |
|  | | |  | | |  | | |
|  | | |  | | |  | | |
|  | | |  | | |  | | |
|  | | |  | | |  | | |
|  | | |  | | |  | | |
|  | | |  | | |  | | |
| Time of Delivery | |  | | |  | |  | |
| Mode of Delivery | | □Vaginal Spontaneous | | | □CS | | □Vaginal Instumental | |
| Indication for CS | | □Failed indution | | | □Abnoral Labor | | □Other | |
|  | | □Abnormal CTG | | | | | | |
| Indication for Assisted | | Vaginal Delivery | | |  | |  | |
| Analgesia | | □Epidural | | |  | |  | |
| PPH | | ml | | | Blood Transfusion | | □ Yes □No | |
| Maternal infection | | □No | | | □Chorioamnionitis | | □Endometritis | |
| Hyperstimulation | | □No □Yes | | | | |  | |
|  | | □ Uterus Rupture | | |  | | □ Placenta Abruption | |
| Other complications  Postpartum Diagnosis | |  | | | Postpartum Stay | | D | |
| Neonatal Birth Wt | |  | | | Apgar Score | | □1min 5min | |
| Neonatal Admission | | □Ward □NICU | | | □No | |  | |
| Indication | | □Infection | | | □Asphyxia | | □MAS | |
|  | | □RDS | | | □Low birth weight | | □HIE | |
|  | | □Other | | | □Neonatal Death | |  | |

Duration of Stay D

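### The comparison of induced with spontaneous labor (aim 3) is non-randomised and matched on two factors only, yet the listed tests are all unadjusted, so a crude difference could not be attributed to induction

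*Protocol*

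**What the plan says.** Section 2 of the Protocol gives as its third aim "Labor patterns of induced vs. spontaneous labor". Section 3 randomises only the balloon arms: "Participants will be randomly allocated to one of four parallel groups, in 1:1:1:1 ratio". Spontaneous labor is not one of them.

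Item 8 of section 3 describes the comparison group. The investigators will "prospectively collect the information of women with spontaneous onset of labor and vaginal delivery in a 1:1 ratio in Nanjing Drum Tower Hospital". Eligibility is restricted: "Women will be eligible as control group if they are nulliparous, singleton pregnancy in vertex presentation, less than 2 cm dilated at admission", with spontaneous onset. There are also exclusions: "We will exclude women who deliver preterm, have fetus with congenital anomalies, or deliver by cesarean section". Matching is on two factors: "Maternal age will be matched and difference of gestational age at delivery should be less than 7 days". The same text recurs in section 6 under data collection for spontaneous labor.

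Section 7 is the only analysis text. It says "For quantitative data, ANOVA or rank sum test will be used", then names chi-square or Fisher tests for categorical data and Kaplan-Meier curves with a log-rank test for time to delivery, all judged at 0.05. It names no regression model or covariate and has no paragraph for aim 3.

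Height, maternal weight and birth weight are on both case report forms. Maternal weight is labelled "Wt before Delivery" in Appendix 2 and simply as weight in Appendix 3.

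**The concern.** Unadjusted tests are sound for the four balloon arms, because randomisation balances the arms in expectation and leaving out covariates costs at most some precision. Aim 3 lacks that protection. A woman is in the induced group because someone found a reason to induce her. The reasons listed in Appendix 2 include FGR, GDM/DM and PIH. The first is defined by fetal size, and the other two are plausibly linked to maternal weight. Controls are not selected on any of these. Matching on maternal age and gestational age does not equalise maternal size or fetal weight.

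If those variables also relate to how labor progresses, the crude contrast mixes their influence with that of induction. A significant result for aim 3 would then show that the two groups labor differently, but not why. The information needed to do better is already being collected and is not put to use.

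**Working it through.** **1. The plan's own figure.** The only computed figure in the Protocol is 126 women per randomised group (section 3, item 7). It reproduces from the stated arcsine formula with λ = 10.903, the noncentrality of a 3-df chi-square test at α = 0.05 and 80% power. The arcsine difference is 2·asin(√0.48) − 2·asin(√0.28) = 1.5308 − 1.1152 = 0.4156, so n = 2 × 10.903 / 0.4156² ≈ 126. That figure concerns the primary outcome only. Aim 3 has no sample size, effect size or power to check.

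**2. What is controlled and what is not.**

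| Factor | Handled by design? | In a section 7 test? | Recorded in both groups? |
|---|---|---|---|
| Maternal age | Matched | No | Yes |
| Gestational age | Matched, within 7 days | No | Yes |
| Maternal height and weight | No | No | Yes |
| Birth weight | No | No | Yes |
| Indication or complication | No | No | Partly: a checklist in Appendix 2, a Complications field in Appendix 3 |

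**3. How large the effect could be.** The documents give neither the imbalance nor the strength of the covariates, so the following is an illustration on assumed values. Take a continuous outcome with no true group difference and one unadjusted covariate.

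- d = difference between groups in the covariate, in SD units (assumed; to be read as what remains after matching).
- r = correlation of the covariate with the outcome (assumed; likewise after matching).
- n per group = 296, the lead-centre target in section 4, if all its women are used 1:1. A smaller case is 140: 296 × 0.95 = 281 nulliparous women (the 95% is from section 3, item 2), of whom about half are assumed to remain after restriction to vaginal births.
- Bias b = d × r. SE = √(2/n), which ignores pairing, as the listed tests do. This gives √(2/296) = 0.082 and √(2/140) = 0.120.
- Rejection rate = Φ(b/SE − 1.96) + Φ(−b/SE − 1.96).

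| d | r | b | n = 296: b/SE | n = 296: rejection | n = 140: b/SE | n = 140: rejection |
|---|---|---|---|---|---|---|
| 0.2 | 0.1 | 0.02 | 0.24 | 5.7% | 0.17 | 5.3% |
| 0.3 | 0.2 | 0.06 | 0.73 | 11.3% | 0.50 | 7.9% |
| 0.5 | 0.3 | 0.15 | 1.82 | 44.6% | 1.25 | 24.1% |

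The bias b does not depend on n. A larger cohort makes the same bias easier to declare significant.

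**The case against.** Four points can be made for the plan.

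- **Section 7 may not govern aim 3.** It never mentions the control cohort, and its intention-to-treat statement has meaning only for randomised women. The method for aim 3 may simply be left open, perhaps to a SAP that is not shown. The text does not settle this. But section 7 is the only analysis text for a protocol with three aims. It lists one set of tests without limiting it to the trial arms, and none of those tests adjusts. If a SAP already has an adjusted analysis, only section 7 needs aligning.
- **The protocol claims no effect of induction.** This stands. A reader might infer a causal claim from the term control group and the p values, but sections 2 and 3 speak only of labor patterns and the progress of labor. For a purely descriptive contrast the crude difference is a legitimate quantity. What cannot be done is to attribute it to induction, and the plan does not say so.
- **The design already removes some confounding.** This also stands. Prolonged gestation is one of the listed indications, and matching gestational age within 7 days handles much of it and constrains birth weight. Restriction to nulliparous, singleton, vertex, early-dilation controls helps too. Neither step balances maternal size, or fetal size at a given gestational age. The direction of any net bias is not established.
- **Control complications are not wholly unrecorded.** One might infer that nothing comparable to the indications is available for controls. Appendix 3 has a Complications field, so a partial comparison is possible.

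**Conclusion.** The point holds as a weakness in a non-primary aim. The groups are not randomised, two factors are matched, every listed test is unadjusted, and three relevant variables are collected in both groups without being used. The randomised comparison and the primary outcome are untouched.

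The size is unknown. On the assumed inputs the false-positive rate of a crude 5% test runs from about 5-6% to about 45%, so the effect may be negligible or large. The upper figure needs a 0.5 SD imbalance, a correlation of 0.3 and all 296 lead-centre women. It should not be quoted as the expected error rate. A reader might also run the calculation with all 504 randomised women. The documents do not support that, because controls are collected 1:1 at the lead centre, whose target is 296, and only vaginal births qualify.

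**What to change.** Add to section 7:

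> For aim 3, labor duration and progress will be compared by a regression model with group (induced or spontaneous), maternal age, gestational age, height, maternal weight and birth weight. The crude comparison is descriptive. Epidural analgesia and oxytocin follow labor onset; they will be reported by group and not adjusted for. Residual confounding by indication remains, and the result will be reported as an association.

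In addition:

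- Use one weight label on both forms. The present labels differ, and Appendix 3 does not say when weight is taken.
- Tabulate the entries in the Appendix 3 Complications field against the induction indications in Appendix 2, by group, so that readers can judge what adjustment cannot remove.

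The cost is a short paragraph, one form label and one table. Neither the sample size nor the randomised analysis changes, and no new data item is needed. The downside is slightly more analysis work and a more cautious conclusion for aim 3.
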